#### **4.6 Comparison group**

During the study period, participants' savings account activity will also be tracked at regular intervals, but they will not be eligible to receive lottery-style prizes. They may instead receive interest on the amount they have saved at a standard rate that is determined by the banking partner.

#### **4.7 Data collection activities**

Structured questionnaires will be administered to all participants at the time of enrollment (baseline) and at study completion. Data will be collected by a team from Innovations for Poverty Action (IPA), which has led a number of household surveys in the Nyanza region. Trained research assistants from IPA will administer these questionnaires using tablet computers. Participants will receive a small amount of compensation for the time required to complete each survey.

*Baseline data collection:* A baseline questionnaire will collect information on demographic characteristics, employment and income, assets and savings, consumption and expenditures, self-reported sexual behavior, alcohol and substance use, HIV risk perceptions, and questions about financial stress, future orientation, and expectations. Sexual behavior questions will inquire about past engagement in transactional sex (defined broadly to include financial and non-financial transfers from the partner to the woman, approximate age of sexual partners).

*Interim data collection:* Additional contact from the survey team may occur at regular intervals during the intervention period. These intermittent contacts may occur via SMS or in person and are expected to take only a few minutes.

*Endline data collection:* An endline survey with similar content as the baseline will be administered about 3-4 months after study enrollment in order to measure economic and health outcomes that have the potential to be affected by the intervention..

The questionnaire modules will be based on questionnaires that have been used in other studies in the Nyanza region and on surveys such as the Demographic and Health Survey and the World Bank's Living Standards Measurement Surveys.

*Qualitative interviews:* In addition to the baseline and endline surveys, we may conduct in-depth interviews with up to 20 men to explore perceptions of the prize-linked savings intervention. Beyond exploring the extent to which the intervention motivated men to save money and change their health and economic behavior, the interviews will also assess other factors that influence men's decisions – including barriers to saving such as beliefs about mortality risks in the future.

#### **4.8 Outcomes**

We will be interested in assessing four primary outcomes:

1. Increase in savings balance: This is a binary variable equal to 1 if the respondent's savings balance increased over the study period, and zero otherwise.
2. Change in savings balance over full study period: Similar to outcome 1, but a continuous measure of the net increase or decrease in savings balance over the study period.
3. Expenditures on alcohol

4. Participation in transactional sex
5. Expenditures on transactional sex

We will additionally assess the following secondary outcomes:

1. Savings: Net increase in both the savings balance and in self-reported total savings from all sources, in each lottery period and over the entire study period.
2. Expenditures on food items
3. Expenditures on non-food items

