## **4.2 Eligibility criteria**

This study will focus on an intervention aimed at changing savings and expenditure patterns, and risk behaviors, among men in communities with high prevalence of transactional sex. Thus we will exclusively recruit men in the pilot phase.

Inclusion criteria:

1. Resident in selected shoreline communities in Siaya County, Kenya
2. Male
3. Age 21 years and above
4. Primary or secondary occupation is fishing or transportation (i.e. motorbike taxi driver)
5. Owns mobile phone
6. Is willing to open a savings account with a local bank

Exclusion criteria:

1. Planning to relocate from study communities in the next 6 months
2. Does not express willingness to open a savings account

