## **4.3 Consent and enrollment processes**

Participants eligible for enrollment in the study will be approached by the study team at the time of the baseline survey and will complete an informed consent procedure immediately prior to the baseline survey. The informed consent form will be distributed to potential participants and will be read aloud (in English, Swahili or Dholuo depending on participant's preference). Survey staff will respond to questions and offer further explanations where necessary, and will ask participants to sign the consent form (or to make a mark, in the case of respondents who cannot write.) For those desiring more time to make a decision, survey staff will leave the consent document with the potential respondent and will follow up on a subsequent day.

Following enrollment in the study, a baseline questionnaire will be administered to all participants (described below). All participants will then be asked to open a savings account with a local banking partner, a process that the study will facilitate. There will be no out-of-pocket cost for participants to open an account and there will be no requirement to deposit their own money into the account.

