## **4.4 Randomization procedures**

Participants will be randomly assigned to either an intervention or control group using simple random assignment. Individuals meeting eligibility criteria and providing consent will be randomized in equal proportions to one of two groups, a control group or an intervention group that receives the prize-linked savings intervention.

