## **4.5 Intervention group**

Research assistant will explain the structure of the lottery prizes to participants randomized to the lottery incentive group. Participants will be told their chance of winning monetary rewards will be based on the amount by which their account balance goes up (e.g. for every 100 Ksh by which savings increases, participants get an entry into a lottery for monetary rewards.) This type of prize-linked savings intervention has been shown to promote savings in other settings. During the intervention period, participants' savings account activity will be checked at regular intervals and lottery prizes will be determined at these intervals. Participants will learn about the lottery outcome via SMS and prizes will be deposited directly into their savings accounts.

Other intervention components may include education materials to explain how the prize-linked savings incentives work and that emphasize the potential benefits of saving money (having greater ability to cope with setbacks, build or upgrade their homes, pay school fees, buy farm

inputs, buy more motorbikes for use in business, or start a different business; etc.). Participants in the intervention group will be encouraged to have more consideration for their future health and economic status, as this may motivate them to save more money. They will also be encouraged to consider the opportunity and health cost of their expenditures on alcohol and transactional sex and not miss the opportunity to win prizes by saving money.

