#### **5.2 Adequacy of protection against risks**

##### **5.2.1 Informed consent**

Informed consent will be obtained from all participants by trained research assistants. Because some participants may not be able to read at a level enabling them to understand the consent form, the survey team will offer to read the letter in its entirety and will discuss the consent process in detail verbally. The research assistants will find a private place; carefully explain the nature and purpose of the study to each potential participant, potential risks and benefits, compensation for participation, and will describe the two study groups to which participants will be randomized. The consent process will be offered in English, Kiswahili, or Dholuo (as per the

participant's preferences). The banking partner will also obtain consent from respondents to share their savings data with study staff. Our study team has prior experience in obtaining informed consent for research and clinical trials within the cultural context of in Kenya. For those who cannot sign the informed consent form, they will be asked to make a mark with the pen or to use an inkpad and make a thumbprint indicating their choice to participate, and a witness will also sign indicating that free and informed consent was given. The informed consent procedure has been designed to maximize understanding of potential risks. Participants will be told that they may decline to participate at any point. The consent procedure will be carried out at baseline, prior to administering the baseline survey. For those who consent, the survey will take place immediately after the consent procedure. For those who are unsure, the survey team will attempt to answer their questions and will work with the potential respondent to find another time on a subsequent day for a follow-up visit.

In order to protect against risks associated with answering sensitive questions, all participants will be reminded that they are not obligated to answer any survey questions that they do not feel comfortable answering.

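### Randomisation does not require an opened account or signed bank data-sharing consent, so men with no observable balance can enter the powered savings outcome

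*Protocol*

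**What the plan says.** **Eligibility and allocation.** The only account-related inclusion criterion in Protocol 4.2 is that the man "Is willing to open a savings account with a local bank". Section 4.4 then states: "Individuals meeting eligibility criteria and providing consent will be randomized in equal proportions to one of two groups".

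**Account and bank data.** Section 4.3 places the account after consent and the baseline questionnaire: "All participants will then be asked to open a savings account with a local banking partner, a process that the study will facilitate". It adds that "there will be no requirement to deposit their own money into the account". Access to the balance depends on a further permission, described in 5.2.1: "The banking partner will also obtain consent from respondents to share their savings data with study staff". No section makes either step a condition of randomisation, or says whether it comes before or after the man learns his arm.

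**Outcome.** Section 4.8 defines outcome 1 as follows: "This is a binary variable equal to 1 if the respondent's savings balance increased over the study period, and zero otherwise". No minimum amount, starting date or opening balance is given. Section 4.8 also lists a secondary savings outcome, "Net increase in both the savings balance and in self-reported total savings from all sources", so the account balance and a man's total savings are treated as separate quantities.

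**Prizes.** In the intervention arm, 4.5 says that "prizes will be deposited directly into their savings accounts". Section 4.8 does not say whether prize money counts towards the increase. Controls cannot win prizes and may instead receive standard interest (4.6).

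**Sample size.** Section 4.9b gives 200 participants for 10% vs 25%, and a detectable difference of at least 16 points with 300 participants and a 50% control rate. It makes no allowance for men without an observable balance.

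**The concern.** The powered outcome exists only for a man who has opened the study account and let the bank share his data. The protocol fixes the population for randomisation one step earlier, at willingness and study consent. Any man lost between the two steps is in the intent-to-treat set (4.9a) with no balance to read.

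Two consequences follow, depending on an order that the protocol leaves open. If the account or the bank consent comes after the man knows his arm, the motive to complete these steps is unequal: an intervention man cannot win without an account, and a control man has no prize to gain. The comparison then mixes account take-up and data access with saving. If these steps come before allocation but are not required, the loss should be balanced, but it still dilutes the effect and the power.

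A further question is what the outcome measures. For a man whose account is new and unfunded, it records whether any money remains at endline. The aim in section 2.0, by contrast, is to shift spending into saving. The pilot is meant to supply effect sizes for a larger trial (4.9b), so an ambiguity here would carry forward.

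**Working it through.** **1. The plan's own figures.** Inputs from 4.4 and 4.9b: 1:1 allocation, 80% power, alpha 0.05. Two-sided testing is assumed because sidedness is not stated. The pooled-variance formula without continuity correction is

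n per arm = [1.96·√(2p̄(1−p̄)) + 0.842·√(p₁(1−p₁)+p₂(1−p₂))]² / (p₂−p₁)²

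- 10% vs 25%: p̄ = 0.175; [1.96·√0.28875 + 0.842·√0.2775]² / 0.0225 = 99.5, so 100 per arm and 200 in total. This matches the plan.
- 50% vs 66%: p̄ = 0.58; [1.96·√0.4872 + 0.842·√0.4744]² / 0.0256 = 148.2, so 149 per arm and 298 in total. This agrees with the stated 300.

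The sample-size arithmetic is sound.

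**2. Equal loss in both arms.** Assume a share m of each arm has no observable balance and is scored 0, while the others follow the planned rates. The rates become (1−m)p₁ and (1−m)p₂, and

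power = Φ{[(1−m)(p₂−p₁)√n − 1.96·√(2p̄(1−p̄))] / √(sum of the two p(1−p))}, using the reduced rates.

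| m (assumed) | 10% vs 25%, n = 100 per arm | 50% vs 66%, n = 150 per arm |
|---|---|---|
| 0 | 15.0 points, power 80.2% | 16.0 points, power 80.5% |
| 5% | 14.3 points, 77.7% | 15.2 points, 75.6% |
| 10% | 13.5 points, 74.9% | 14.4 points, 70.6% |
| 20% | 12.0 points, 68.9% | 12.8 points, 60.5% |
| 30% | 10.5 points, 62.1% | 11.2 points, 50.6% |

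**3. Unequal loss and no true effect.** Assume the same saving rate p in both arms, and that men without data would have saved at that same rate. Scored rate = p·(1 − unavailable share), so the false difference is p × (control share − intervention share).

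| Unavailable, control vs intervention (assumed) | p = 10% | p = 50% |
|---|---|---|
| Equal | 0 | 0 |
| 10% vs 2% | 9.0% vs 9.8%: 0.8 points | 45% vs 49%: 4 points |
| 15% vs 5% | 8.5% vs 9.5%: 1.0 point | 42.5% vs 47.5%: 5 points |

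At 15% vs 5%, 5 points is 5/16, about a third, of the 16-point detectable difference. One point is 1/15 of the 15-point target.

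**4. What a score of 1 means.** The opening balance is not stated; assume zero or nominal, since no deposit of own money is required. An increase then means that the endline balance exceeds the opening balance by any amount. Prizes are paid into the same account, so a man who withdraws all his own money but leaves a prize in place would also score 1. This can happen only in the intervention arm.

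**The case against.** The strongest reply is that the protocol is silent here rather than wrong, and that its layout may already imply the right order: account opening is in 4.3, randomisation in 4.4, and explanation of the lottery in 4.5. That is fair. If section order is the real order, arm-related uptake largely disappears. But section order is not a rule, 4.4 does not make the account or bank consent a condition, and the power loss in the second step of the working remains.

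Several stronger readings are tempting but not supported:

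- **That every man starts at zero and his balance cannot fall.** Section 4.3 says participants are asked to open an account. The opening balance is not given, and men who already bank with the partner are not excluded. The allowance for a decrease in outcome 2 is therefore not a contradiction.
- **That the plan counts unavailable data as non-saving.** The outcome wording is ordinary coding of a 0/1 variable, not a missing-data rule. That rule may sit in an analysis plan not shown here. A man who never opens an account has no increased balance, so scoring him 0 is defensible under intent-to-treat. The clear misclassification is the man who saves in the account but withholds his bank data.
- **That a minimum deposit is needed.** This is a preference. Outcome 2 already measures the amount, the spending outcomes are also primary, and total savings is secondary.
- **That prizes drive the result.** Section 5.3 expects few winners, drawn from men who increased their savings. The point is only that prizes are not excluded.

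The unavailable shares used above have no source in the protocol, and the false difference is small at the 10% control rate.

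**Conclusion.** The concern holds in a limited form. The protocol lets men be randomised before it is assured that the powered outcome can be observed, and it does not state when account opening and bank consent occur relative to disclosure of the arm. It is not shown that bias will occur.

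If these steps follow allocation and unavailability is 15% vs 5%, the false difference is between 1 point (10% saving rate) and 5 points (50% saving rate). If unavailability is equal at 20%, there is no false difference, but power drops to 68.9% or 60.5% under the two planning scenarios. All these figures rest on assumed shares and on scoring the affected men as zero. The stated sample sizes themselves are correct.

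Separately, outcome 1 is better described as use of the study account than as increased saving. That reading assumes a new account with a zero or nominal opening balance. The correction is worth making because it is cheap and because the order of enrolment steps cannot be repaired at the analysis stage.

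**What to change.** 1. **Sections 4.3 and 4.4:** state one sequence and make each step a condition of the next: study consent, baseline survey, account opened, bank data-sharing consent signed, then randomisation and disclosure of the arm.
2. **Section 4.8, outcome 1:** define it on the participant's own deposits net of withdrawals, excluding prizes and interest, from a stated opening balance and start date. Add a rule for withdrawals of prize money. Report it as use of the study account, not as increased total saving.
3. **Optional, and suitable for the analysis plan:** any minimum net deposit, and how an unavailable balance is coded.

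**Cost.** There will be a short delay between consent and allocation while the account is opened. Some willing men will be lost before randomisation, so the results will apply to men who opened an account and agreed to share its data. The number lost at each step should be reported; it is useful feasibility information for a pilot.

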**The rapid expansion of mobile phone ownership in Africa has also led to increased access to financial services among the poor.** In the past 10 years, mobile phone companies began to offer a “mobile money” service in which people who own a cell phone number could deposit, withdraw and transfer money simply by visiting a local “cash point” (in rural areas, this is typically a kiosk in villages). Essentially, this made it easier for individuals to save money and send money to each other, with kiosks where people typically buy vouchers to top up their phone credit serving as bank branches. Use of mobile money services is now ubiquitous in Kenya due to the early introduction of the *M-Pesa* service by Safaricom, a leading mobile phone company.[7, 8] The services were used by 96% of Kenyan households and there were 110,000 “cash points” in the country (as compared to only 2,700 bank ATMs). Mobile money is now widely used in nearly all developing countries.[9] A recent study in *Science* showed that expansion of mobile money in Kenya contributed significantly to poverty alleviation, and that it led to increased financial resilience and occupational choice.[7] This expansion of mobile phone ownership and mobile money has induced banks to provide a wider array of savings products targeted at previously unbanked individuals and communities. Many banks now offer savings accounts in which deposits and withdrawals can be made by using mobile money, rather than visiting physical branch offices of the banks.

**With the widespread availability of savings accounts in Kenya and other countries, there is an opportunity to deploy novel interventions that promote public health objectives.** To our knowledge, no studies have sought to use savings accounts to influence men's spending on risk factors for HIV such as alcohol and transactional sex. *We propose to use prize-linked savings accounts as a vehicle for a novel intervention that will encourage men to alter their expenditure patterns and save more money.* Our theoretical rationale is that when offered incentives to save money, men will save more of their income and spend less on alcohol and transactional sex. There are other ways in which incentivizing saving may reduce sexual risk

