### **3.0 STUDY DESIGN**

#### **3.1 Overview of study design**

We will develop a researcher-implemented prize-linked savings intervention that is linked to participants' savings account balances. We will develop a system of lottery-based rewards that participants can win depending on how much their account balance goes up (e.g. for every 100 Ksh by which savings increases, participants get an entry into a lottery in which there is a chance of winning monetary rewards). We may also consider other ways to structure rewards for saving and explore the potential for interventions to build future-orientation among men. Participants in the study will be randomized to a control group or an intervention group that receives the prize-linked savings intervention.

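### Primary savings outcomes 1 and 2 read the same account balance that earns lottery entries in one arm only, so money moved in and prizes paid in count as saving

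*Protocol*

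**What the plan says.** Section 4.8 lists two primary outcomes on savings. Outcome 1: "This is a binary variable equal to 1 if the respondent's savings balance increased over the study period, and zero otherwise". Outcome 2 is "a continuous measure of the net increase or decrease in savings balance over the study period". The first secondary outcome is "Net increase in both the savings balance and in self-reported total savings from all sources, in each lottery period and over the entire study period". The protocol does not define the savings balance expressly. The contrast with all sources in the secondary outcome, and the account tracking described in sections 4.3, 4.5 and 4.6, point to the account opened with the banking partner.

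Sections 3.1 and 4.5 reward that same balance. As the example in 3.1 puts it, "for every 100 Ksh by which savings increases, participants get an entry into a lottery"; in 4.5, the "chance of winning monetary rewards will be based on the amount by which their account balance goes up". Section 4.5 adds that "prizes will be deposited directly into their savings accounts". Under section 4.6, controls are tracked in the same way but receive no prizes, at most the bank's standard interest.

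Section 4.9b sizes the trial on outcome 1 and describes a difference in that outcome as a difference in the probability that savings increase. On money held elsewhere, section 1.0 says of mobile money: "The services were used by 96% of Kenyan households". It adds that many banks accept deposits and withdrawals through it without a branch visit.

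**The concern.** The Abstract and section 2.0 ask whether the incentive shifts income from alcohol and transactional sex into saving. An account balance can rise for three reasons: new saving, transfer of money already held elsewhere, or a prize paid in. Outcomes 1 and 2 do not separate these. Only the intervention arm is paid to transfer money and only that arm receives prizes, so both distortions act on the between-arm difference. Randomization cannot remove them, because the incentive to transfer is part of the treatment.

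Outcome 1 is the more exposed to transfers. It has no minimum amount, and section 4.3 requires no deposit of the participant's own money at opening, so one small transfer that stays in the account turns a 0 into a 1.

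At stake is how a positive result on the powered outcome is read. It could be carried into the larger trial as evidence that men saved more, when they had only changed where they keep money.

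**Working it through.** **Inputs.** From section 4.9b: 80% power, alpha 0.05; 200 men for a 15-point rise from a 10% control rate; 300 men and a 16-point difference at a 50% control rate. From section 4.4: equal allocation. Two-sided testing is assumed, since sidedness is not stated.

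**Step 1: reproduce the plan's figures.** With pooled variance and no continuity correction, the number per arm is

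n = [1.96·√(2p̄(1−p̄)) + 0.842·√(p0(1−p0) + p1(1−p1))]² / (p1−p0)², where p̄ = (p0+p1)/2.

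- 10% v 25%: (1.96 × 0.5374 + 0.842 × 0.5268)² / 0.0225 = 99.5, so 100 per arm and 200 in total. The stated figure is 200.
- 50% v 66%: (1.96 × 0.6980 + 0.842 × 0.6888)² / 0.0256 = 148.2, so 149 per arm and 298 in total. The stated figure is 300; power at 150 per arm is 80.5%.

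The sample size arithmetic is sound and is not in dispute.

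**Step 2: the difference that transfer alone would create.** Suppose total savings are unchanged by the intervention. Suppose also that a share s of the intervention men whose balance would otherwise not have risen move existing money in and leave it there to the final reading. The share s is an assumption; the documents give no value. Then

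p1 = p0 + (1 − p0)·s, and the spurious difference is (1 − p0)·s.

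- Control rate 50%, 150 per arm: 0.16 = 0.50·s, so s = 32%. In men, 0.16 × 150 = 24, out of 75 who would otherwise show no rise.
- Control rate 10%, 100 per arm: 0.15 = 0.90·s, so s = 16.7%, about one in six. In men, 15 out of 90.

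**Step 3: range over s.** Chance of a significant result on outcome 1 with no new saving:

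| Control rate | Per arm | s | Intervention rate | Chance of significance |
|---|---|---|---|---|
| 10% | 100 | 5% | 14.5% | 16% |
| 10% | 100 | 10% | 19% | 44% |
| 10% | 100 | 16.7% | 25% | 80% |
| 50% | 150 | 10% | 55% | 14% |
| 50% | 150 | 20% | 60% | 41% |
| 50% | 150 | 30% | 65% | 75% |
| 50% | 150 | 32% | 66% | 80% |

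**Step 4: prizes.** Prize money adds directly to outcome 2 in the intervention arm while it stays in the account. Section 9.0 budgets USD 404.39 for intervention costs. If all of it were prizes, which is not stated, the mean would be 404.39 / 150 = USD 2.70 per intervention man. For outcome 1 the route is narrower. Section 5.3 gives prizes only to men whose savings increased, so a winner has usually already shown a rise. The prize changes his final score only if he later takes out his own money and leaves the prize in.

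**The case against.** Several stronger readings are tempting, and the documents do not support them.

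- **That saving is judged only on the study account.** All-source savings is a named secondary outcome. Section 4.7 collects assets and savings at baseline, with similar content at endline. The issue is its rank and its lack of a link to the primary conclusion.
- **That a failure to shift spending would go unseen.** Alcohol expenditure, participation in transactional sex and expenditure on it are themselves primary outcomes. If men only relabelled money, these would be expected to show no effect. The safeguard is partial: section 4.9b concedes that power may be lacking on some primary outcomes, so a null there can be put down to sample size.
- **That transfer by 16% of the men who would otherwise show no rise gives 16 points.** At a 50% control rate that share gives 0.50 × 0.16 = 8 points, with about 28% power at 150 per arm. The 16% is a share of the whole arm.
- **That parking money around each lottery check inflates the primary outcomes.** Outcomes 1 and 2 cover the full study period, so own money put in and taken out again nets to zero. Parking mainly affects the per-lottery-period secondary measure, and reaches the primaries only at the final reading or through a prize left behind.
- **That relabelling will be widespread.** The 96% figure is household use of mobile money, not savings held there, and section 1.0 describes communities with low savings rates.
- **That outcome 2 should give way to total savings.** Self-report is noisier and may be inflated in an arm that section 4.5 encourages to save.

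It is also fair to say that account response is a reasonable endpoint for a pilot, and that an analysis plan not seen here may add an interpretation rule. What stands is that the protocol fixes its primary savings outcomes on the rewarded quantity and then calls a rise in it a rise in savings.

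**Conclusion.** The point holds as a question of what outcomes 1 and 2 measure. They capture response in the account, in which new saving, transferred money and prizes are mixed, and only the intervention arm has a reason for the second and a source of the third. They do not by themselves support a conclusion that saving increased.

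The size cannot be estimated from the documents. The calculations show vulnerability only: transfer by about a third of would-be non-risers at a 50% control rate, or a sixth at 10%, would match the whole design effect, while a 10% share would leave a significant result well short of assured (14% and 44%). This rests on reading the savings balance as the study account, on transferred money still being there at the end, and on no change in total savings. The change is worth making before the analysis, because it determines what a positive result may be called.

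**What to change.** 1. Keep outcomes 1 and 2 as bank-recorded primary outcomes. State that they refer to the study account, compute them on the participant's own money (balance net of prize deposits), and describe them as account saving.
2. State how withdrawals after a win are treated. Subtracting every prize in full penalises a winner who has already withdrawn it; treating withdrawals as prize money first does not. Choose one as the rule and report the other as a check. If interest is paid to controls, remove it on the same principle.
3. Report the change in all-source total savings, from the baseline and endline surveys, beside outcomes 1 and 2.
4. State that the intervention will be said to have increased saving only if the total-savings estimate is in the same direction as the account result. Otherwise report a rise in account use.

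**Cost.** The surveys and account tracking are already planned. The additions are a record of prize deposits and withdrawals by participant, and a few sentences in sections 4.8 and 4.9a. Stated sample sizes need not change on this account. The drawback is that total savings is self-reported, noisy and possibly inflated in the encouraged arm. Agreement in direction is therefore a modest safeguard: it should qualify the bank-based result and not replace it.
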